### Objectives

Due to the uniqueness of the Rostock Longitudinal Study (“ROstocker LängsschnittStudie,” ROLS) in terms of its duration, research focus, and the lack of comparable studies, many of the investigations presented here are exploratory in nature. Our work will start with longitudinal analysis of data on coping. (1) Using data from previous measuring points, we will identify qualitatively distinct coping profiles across three decades of adulthood and examine probabilistic transitions between these profiles over time. Moreover, we will evaluate whether certain profiles are associated with more favourable or adverse mental health and well-being outcomes in late middle age. (2) We will assess the role of these lifelong coping profiles in buffering or facilitating the effects of COVID-19-related restrictions, exploring whether certain profiles are linked to more or less psychopathological strain. (3) Similarly, we plan to characterise longitudinal trajectories of alcohol use to cope, examining differences in intercepts and slopes, and investigate whether trajectory membership of drinking alcohol to cope motives predicts actual alcohol consumption during the COVID-19 pandemic. To extend this developmental coping perspective, we will examine neurobehavioural and social factors that may shape individual differences in stress regulation and health-related coping during a prolonged public health crisis. (4) Specifically, we will investigate the neurobehavioural basis of stress regulation during the COVID-19 pandemic by testing whether ventromedial prefrontal control and mesostriatal reward anticipation are associated with psychopathological COVID-19 strain over time, and whether these associations are mediated by self-reported control strategies. (5) We will examine the role of social integration in coping with COVID-19 by analysing egocentric social networks to assess how network structure and behavioural composition relate to health-related coping and preventive behaviours during the pandemic. (6) Lastly, the accentuation hypothesis will be tested by examining change in variability in outcomes, assessing stability in individuals’ rank positions over time, and analysing the direction and magnitude of individual changes. Shifts towards distributional extremes versus the centre will distinguish accentuation from regression to the mean and will be modelled using regression analyses with coping trajectories and multidomain predictors.

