### Sample size

The study is embedded in a closed longitudinal cohort that has been followed for over 50 years. Consequently, the expected sample size is determined by cohort availability and participants’ willingness to take part at the time of data collection, rather than by recruitment targets. The data collection phase of the 8th wave took place between 2006 and 2009. Out of originally 294 mother–child pairs, 211 participants took part (71% retention rate after almost 40 years). Given the long follow-up interval, expected age-related attrition, and loss to follow-up typical of long-term cohort studies, a reduction in participation is anticipated. In addition, the current wave includes assessments related to COVID-19–related experiences, which represent a potentially sensitive topic and may further affect participation rates. Based on these considerations and prior participation patterns, we expect to recruit approximately 150 participants in the current wave (~50% retention rate after 55 years). All eligible participants will be systematically contacted and invited to participate using repeated and respectful procedures. At the beginning of recruitment in February 2022, participants were around 52 years old. Data collection started in April 2022. At the time of submission of the study protocol, data of 103 individuals have been collected. We expect a subsample size of 50% for blood sampling and imaging procedures as they are unfamiliar to our participants and may be met with hesitation.

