Data of the 9th wave will be analysed once participants have completed all study parts and no interim analysis will be performed. The data collection process will be terminated, when all participants expressing interest in participation are met in person. As for the analysis of the hypotheses mentioned above, methods will be the following: (1) Coping profiles and their trajectory across adulthood will be analysed using latent profile transition analysis implemented as a hidden Markov model. Habitual coping, assessed consistently with the Stress Management Questionnaire (72) at three time points (6th, 8th, and 9th waves), will be used to identify qualitatively distinct profiles and probabilistic transitions over three decades, whilst accounting for measurement error. This person-centred approach is appropriate considering the theoretical interest in stable and changing patterns of coping rather than continuous change in individual strategies. Given three waves over decades, we will use Full Information Maximum Likelihood (FIML) to handle missing data. Post-hoc profiling of coping trajectories and their associations with health and well-being in late middle age will include analyses of variance and appropriate non-parametric alternatives. (2) The role of lifelong coping profiles during the COVID-19 pandemic will be investigated using linear mixed-effects models (LMMs) with monthly psychosocial strain ratings (on a Likert-type scale ranging from 1 to 5) over 3 years of the pandemic (March 2020 to March 2023) as the outcome. To address potential memory bias during retrospective data collection, participants are given brief descriptions of currently valid COVID-19 restrictions for each month. Coping profile membership will be included as a fixed effect, with piecewise time segments representing stricter versus less restrictive pandemic periods. Random intercepts and random slopes for time will model baseline differences and individual variation in trajectories. To account for varying recall periods between the month being rated and survey completion, recall delay (in weeks) will be included as a covariate in all LMMs. Interactions between coping profiles and piecewise time will test whether certain profiles buffer or exacerbate psychosocial strain. (3) Alcohol use to cope trajectories from emerging adulthood to late middle age will be analysed using latent growth mixture modelling on the alcohol-related items of the subscale substance use to cope (Stress Management Questionnaire) for three time points (6th, 8th, and 9th waves), missing data will be handled using FIML. Trajectory membership will be used to predict alcohol consumption during the COVID-19 pandemic by fitting linear regression models, and potential sex effects will be explored using the three step approach with multinomial logistic regression models. Whilst the identification of coping and alcohol-use trajectories across adulthood is primarily exploratory given the uniqueness of the cohort and the absence of comparable long-term studies (Objectives 1–3), the investigation of neurobehavioural and social influences on coping during the COVID-19 pandemic (Objectives 4–6) is theory-guided and builds on prior evidence regarding stress regulation, executive control, reward processing, and social integration. (4) Functional MRI data will be analysed using standard pipelines in SPM, running in MATLAB, including standard preprocessing. For task-based fMRI, individual-level contrasts for the onset of event types will be modelled and general linear models (GLMs) will be specified for the Stop Signal Task (Go, Successful Stop, Failed Stop) and Monetary Incentive Delay task (cue, anticipation, outcome), with regressors convolved with the canonical hemodynamic response function. At the group level, we will extract activation measures from regions of interest, including ventromedial prefrontal cortex (vmPFC) for cognitive control and mesostriatal regions for reward anticipation that will first be examined as predictors of longitudinal psychopathological strain during the COVID-19 pandemic using linear mixed-effects models (LMMs). Monthly strain ratings will serve as the outcome, with ventromedial prefrontal cortex activation (Stop Signal Task) and mesostriatal reward anticipation (Monetary Incentive Delay task) included as time-invariant predictors. Piecewise time segments representing periods of stricter versus less restrictive measures will be specified, along with random intercepts and random slopes for time, to model individual differences in baseline strain and trajectories. Interactions between neural activation and time will be tested to assess buffering or vulnerability effects across pandemic phases. In a second step, self-reported control strategies as assessed with the Optimisation in Primary and Secondary Control Scale (73) during the pandemic will be examined as potential mediators of the association between neural activation and psychopathological strain. Mediation analyses will be conducted using multilevel mediation models, with neural activation predicting control strategies and control strategies predicting longitudinal strain, whilst accounting for the repeated-measures structure of the outcome. Indirect effects will be estimated using appropriate methods for multilevel data (e.g., Monte Carlo or bootstrapped confidence intervals), allowing evaluation of whether neurobehavioural markers influence pandemic-related strain through engagement in specific coping strategies. MPRAGE, resting state, and DTI data will be analysed by the consortium later on. (5) Social network analysis will consist of an examination of key egocentric metrics—including network size, density, degree centrality, and constraint—that will be calculated and visualised using R with the *igraph* and *egor* packages, or Network Canvas’s built-in analytics. Alter-level data on vaccination behaviour, adherence to COVID-19 restrictions, and health behaviours relevant to coping (e.g., physical activity, alcohol consumption) will be used to characterise the behavioural composition of each ego network. In a second step, Exponential Random Graph Models (ERGMs) for small networks (*ergmito*) (74) will be fitted to investigate homophily in vaccination and clustering in preventive and health-related behaviour during the COVID-19 pandemic, using exact statistical calculations instead of simulation-based approximations. Separate models will be specified for vaccination and restriction adherence as well as for health behaviours conceptualised as coping efforts (e.g., exercise, alcohol use). These analyses will test whether similarity in health-related coping behaviours is greater than expected by chance and whether socially embedded behavioural patterns contribute to adaptive or maladaptive coping during a health crisis. (6) For the accentuation hypothesis, several ways will be tested to verify it. First, deviations in panel samples should increase for several outcomes, such as alcohol consumption or positive health behaviour. If deviations increase within the health behaviour data, the hypothesis should be tested that persons remain stable with regard to their ranks in outcomes before and during or after the crisis. In a third approach, individual changes in different outcome measures should be analysed for their direction and magnitude. Changes towards the edges of distributions will speak for the accentuation hypothesis, changes towards the centre for a regression to the mean. Changes of both kinds will then be modelled as the dependent variable in several regression models including coping trajectories mentioned above and predictors from various domains, such as social relations, COVID-associated burdens, brain associated mechanisms or genetic risks (PRS). Analyses were restricted to measures relevant to the predefined research questions of the ROLS and other harmonised measures are reserved for future consortium analyses.

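### Objective 3 speaks of predicting pandemic drinking, but its trajectory classes include drinking-to-cope answers from wave 9, given during or after the outcome period

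*Protocol article*

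**What the plan says.** The Objectives section sets the aim as to "investigate whether trajectory membership of drinking alcohol to cope motives predicts actual alcohol consumption during the COVID-19 pandemic". In the Data analysis section, item (3), the trajectories are fitted by latent growth mixture modelling to the "alcohol-related items of the subscale substance use to cope (Stress Management Questionnaire) for three time points (6th, 8th, and 9th waves"), with FIML for missing values. Then: "Trajectory membership will be used to predict alcohol consumption during the COVID-19 pandemic by fitting linear regression models". Sex is the only other variable mentioned for this item.

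Three dates matter.
- Sample size section, on wave 9: "Data collection started in April 2022".
- Sample size section, on the last wave before the pandemic: "The data collection phase of the 8th wave took place between 2006 and 2009".
- Data analysis section, item (2), on the monthly strain ratings: "over 3 years of the pandemic (March 2020 to March 2023) as the outcome". No window is given for alcohol consumption.

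Item (6) examines outcomes that include alcohol consumption, asks whether "persons remain stable with regard to their ranks in outcomes before and during or after the crisis", and then regresses individual change on the coping trajectories and other predictors. The article calls Objectives 1 to 3 primarily exploratory.

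**The concern.** A predictor should be fixed before the outcome occurs. Here one of the three measurements that define the class is taken when most or all of the outcome period has passed, and it asks about closely related behaviour. Someone whose drinking rose in 2020 or 2021, and who says so on the wave-9 coping items, can be placed in a high or rising class because of that drinking. The regression then partly relates pandemic drinking to itself. For people missing wave 6 or wave 8, FIML bases the classification more heavily on wave 9.

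At stake is the wording of the result. A claim that lifelong drinking-to-cope predicts how people drank in the crisis needs a predictor measured before the crisis. The problem may also spread, because item (6) reuses coping trajectories to explain change. Whether that means the Objective 1 profiles or the Objective 3 trajectories, both are built from waves 6, 8 and 9.

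**Working it through.** **1. Time order (dates from the article).** Wave 6 was in 1990, wave 8 in 2006 to 2009, and wave 9 from April 2022. No wave lies between wave 8 and wave 9, so cohort data on drinking during the pandemic must come from wave 9. Assume the alcohol window equals the strain window, March 2020 to March 2023, which is 37 calendar months. March 2020 to March 2022 inclusive is 25 months, and 25/37 = 68%. That share of the window had passed before the first wave-9 answer. For anyone seen after March 2023 the whole window had passed.

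**2. Is there a planned figure to reproduce?** Not for Objective 3: no effect size or power is stated. The expected sample of about 150 reproduces as 150/294 = 51%, against about 50% stated.

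**3. Illustrative simulation (all inputs assumed).** There were 3,000 datasets of 150 per scenario, tested two-sided at 5%, with no effect of coping motive on pandemic drinking. A stable habit explains 30%, 50% or 70% of consumption variance and 20% or 40% of item variance. A pandemic-period state shared by wave-9 items and pandemic drinking explains 0% or 20%. Class is the top third of the summed items, a stand-in for growth-mixture classes. Ranges are over the 12 scenarios.

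| Predictor and model | Class difference (SD) | Significant |
|---|---|---|
| Waves 6, 8, 9; unadjusted | 0.58 to 1.25 | 94 to 100% |
| Waves 6, 8; unadjusted | 0.51 to 1.03 | 85 to 100% |
| Waves 6, 8, 9; adjusted for earlier consumption | 0.33 to 0.76 | 68 to 100% |
| Waves 6, 8; adjusted | 0.27 to 0.53 | 54 to 91% |

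The wave-9 part can be isolated. With the shared state at 20%, adding wave 9 to the unadjusted predictor raises the difference by 0.20 to 0.26 SD (for example 0.74 − 0.51 = 0.23). With the state at 0% it still raises it by 0.05 to 0.11 SD (for example 0.58 − 0.51 = 0.07), because a third item measures habit better. The part due to the shared state is the three-wave difference with the state less that without it: 0.74 − 0.58 = 0.16, and 0.14 to 0.16 SD across all six pairs.

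**4. What adjustment does.** Making both changes cuts the class difference by between 28% (0.72 to 0.52) and 73% (1.05 to 0.28). It does not reach zero, because a single noisy consumption measure captures habit only partly.

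**5. Precision.** Assume a correlation of 0.4 between predictor and earlier consumption, consumption stability of 0.6, and no direct effect.
- Unadjusted correlation of predictor with outcome: 0.4 × 0.6 = 0.24.
- Residual variance: 1 − 0.24² = 0.942 unadjusted; 1 − 0.6² = 0.64 adjusted.
- Variance inflation from the correlated covariate: 1/(1 − 0.4²) = 1/0.84.
- Standard-error ratio: √(0.64/0.84) / √0.942 = 0.873/0.971 = 0.90.

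The gain is about 10%. For correlations of 0.3 to 0.5 and stabilities of 0.5 to 0.7 it runs from a 23% reduction to a 3% increase.

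**The case against.** The strongest defence is that the objective concerns the level of drinking during the pandemic, within an exploratory programme that looks for lasting coping patterns. On that reading, a stable habit that carries into 2020 is an answer and not an artefact. The questionnaire is also described as measuring habitual coping, so wave-9 answers may reflect disposition more than recent drinking; the scenarios with no shared state represent that case. Dropping wave 9 also loses late middle age, which the trajectories are meant to cover.

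Much of this stands. A reader might infer that the plan ignores earlier consumption and will present stable habits as pandemic coping. The documents do not support that:
- The aim is stated as a level, not a pandemic-induced change.
- The article gives no covariate list for this regression, and a condensed article may leave one to the full protocol or analysis plan.
- Item (6) separately models change, with coping trajectories as predictors.
- An earlier consumption measure is implied by the comparison in item (6), but it is not named or tied to wave 8.

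The defence does not reach the timing. Wave 9 is in the predictor by explicit statement, and no covariate list alters when those items were answered. Whether the answers are purely dispositional cannot be assumed in a study that asks how a crisis changes behaviour.

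**Conclusion.** The point holds as one of time order and wording. Objective 3 claims prediction, but its predictor contains information recorded during or after the outcome period, so pandemic drinking can influence class membership. This follows from the article's own dates. The 25-of-37-month figure also assumes that the alcohol window matches the strain window.

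The size is not known. Under the assumed 20% shared state the contamination is 0.14 to 0.16 SD, and with no shared state it is nil. The larger differences in the simulation come mainly from stable habit. They bear on the plan only if someone reads the association as specific to the pandemic, and the article does not make that claim for Objective 3. Any precision gain from adjustment is modest and not assured. The plan should be corrected before the wave-9 analysis, but the descriptive part of the objective is unaffected.

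**What to change.** 1. For the predictive regression, use pre-pandemic information only: wave-6 and wave-8 drinking-to-cope scores, entered as level and change. Two waves cannot support the growth mixture, so scores should replace classes here.
2. Keep the three-wave growth mixture as the descriptive result. If its classes are related to pandemic drinking, call that a concurrent association.
3. Where an earlier consumption measure exists, report a model adjusted for it beside the unadjusted one before reading any association as pandemic-specific. This moves the question from level towards change. If early drinking-to-cope raised later consumption, adjustment also removes part of the lifelong effect. Control is partial, because the last pre-pandemic wave lies 11 to 14 calendar years before 2020.
4. In item (6), state which trajectories enter the change models and apply the same rule on wave 9.

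The cost is small. The items for step 1 are already held; step 3 depends on an earlier consumption measure being available. The predictor no longer covers late middle age. Persons missing wave 6 or wave 8 need a stated method: 294 − 211 = 83 of the cohort did not take part at wave 8, though how many of them join wave 9 is not given. FIML is specified for the trajectory model ("for three time points (6th, 8th, and 9th waves), missing data will be handled using FIML"), but elsewhere the article lists it only as one option, so its use in this regression should be stated.

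### Objective 4: the mediation paths as written carry no strategy-by-period term, so a buffering effect found in step one has no mediation test

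*Protocol article*

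**What the plan says.** Under Objectives, item (4) asks whether two activation measures "are associated with psychopathological COVID-19 strain over time", and "whether these associations are mediated by self-reported control strategies".

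Data analysis, item (4), answers in two steps. Step one is a linear mixed model for the monthly ratings with piecewise time segments for stricter and looser periods, person-specific intercepts and slopes, and the activation measures "included as time-invariant predictors". It adds: "Interactions between neural activation and time will be tested to assess buffering or vulnerability effects across pandemic phases".

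Step two takes as mediator the "self-reported control strategies as assessed with the Optimisation in Primary and Secondary Control Scale (73) during the pandemic". The models are multilevel, "with neural activation predicting control strategies and control strategies predicting longitudinal strain, whilst accounting for the repeated-measures structure of the outcome". The indirect effects get Monte Carlo or bootstrap intervals, "allowing evaluation of whether neurobehavioural markers influence pandemic-related strain through engagement in specific coping strategies".

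Item (2) of the same section describes the monthly ratings: a 1-to-5 scale from March 2020 to March 2023, with each month cued by a short description of the restrictions then in force. For Objective 2, the test of whether coping profiles buffer strain is a profile-by-time interaction.

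**The concern.** Step one separates the level of strain from its change between periods and defines buffering as the change. Step two names one path into the mediator and one path from mediator to strain, and neither involves time. Accounting for repeated measures handles the correlation among a person's ratings. It does not make the mediator's effect differ between periods.

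Two things are at stake. If activation relates to strain only through its interaction with the period, the mediation as written cannot show what carries that effect. And if the indirect effect is on level alone, a stable tendency to distress that goes along with both activation and control style can produce it without any differential response to restrictions. The result would then be open to being read as a mediated response to the pandemic measures.

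**Working it through.** **1. Structure.** Let X be activation, M control strategies, Y monthly strain, and S the stricter-period indicator, centred at its mean over the rated months. The paths as written are

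- M_i = a·X_i + error
- Y_it = g0 + g1·S_t + c·X_i + b·M_i + u0_i + u1_i·S_t + error

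The indirect effect in month t is a·b, whatever S_t is. Random slopes u1_i do not alter this, nor does an X-by-S term in the outcome equation, because neither lets b vary with S. With interactions the outcome equation becomes

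- Y_it = g0 + g1·S_t + c0·X_i + c1·X_i·S_t + b0·M_i + b1·M_i·S_t + u0_i + u1_i·S_t + error

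The indirect effect in month t is then a·(b0 + b1·S_t). Averaged over the rated months it is a·b0; the stricter-minus-looser difference is a·b1. Only a·b1 mediates the buffering effect tested in step one.

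**2. Inputs from the article.** Imaging sample (Sample size): 50% of about 150, so 0.5 × 150 = 75. Months: March 2020 to March 2023 with both ends counted, 10 + 12 + 12 + 3 = 37. The article gives no power, effect size or correlation for Objective 4, so there is no figure of its own to reproduce.

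**3. Illustration, on assumed values.** 1,000 simulated studies per setting; 37 months, 14 of them taken as stricter; SDs of 0.5 for person level, 0.3 for person-specific phase change and 0.7 for monthly error; Monte Carlo 95% intervals. The level version used each person's mean strain, the phase version the stricter-minus-looser difference.

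*Stable trait only, no true mediation.* The trait loads equally on activation and strategies and shifts strain by 0.5 points per SD in all months. The implied activation–strategy correlation is the squared loading.

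| Loading | Implied correlation | Level version significant, n = 75 | Phase version significant, n = 75 |
|---|---|---|---|
| 0.3 | 0.09 | 3.8% | 1.0% |
| 0.5 | 0.25 | 41.2% | 2.8% |
| 0.7 | 0.49 | 83.4% | 5.7% |

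The mean spurious indirect effect on level was 0.013, 0.049 and 0.115 scale points per SD of activation. At n = 150 the level version was significant in 10.8%, 82.2% and 99.1% of studies and the phase version in 0.7%, 5.4% and 4.3%, so a larger sample does not cure the problem.

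*Mediation of phase change only.* Strategies shift the stricter-minus-looser difference by 0.2 points per SD, and a = 0.3 or 0.5, so the true a·b1 is 0.3 × 0.2 = 0.06 or 0.5 × 0.2 = 0.10. At n = 75 the level version was significant in 4.5% and 6.0% of studies, about the nominal error rate. The phase version was significant in 74.8% and 96.4%. These last two figures are not power estimates for this study, since they depend on the assumed effect and the small assumed SD of phase change.

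**The case against.** The strongest reply is that an unlisted term is not an excluded one. Step one calls its outcome longitudinal strain, and step two uses the same term inside multilevel models. The Objectives refer back to associations over time. Read together, step two could inherit the full step-one model, and an article need not list every coefficient. This stands in part: the wording does not rule out a trajectory effect, so a reader who infers that the plan explains the level and not the change goes further than the text. But the article does list step one's interactions and step two's paths, and for Objective 2 it names the coping-by-time term that makes coping a buffer. That term is absent where coping becomes the mediator.

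A reader might also infer that general distress-proneness will be reported as mediation of pandemic-related strain. The documents do not support that. All ratings fall within the pandemic and are cued by each month's restrictions, so their level is not simply general distress. The size of any spurious effect rests on correlations the article does not give, and at a loading of 0.3 it is rare. The plan also speaks of potential mediators and of evaluating whether an effect exists.

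A single strategy measurement per person is likewise inferred: the article says only that the scale refers to the pandemic, and the supplement describing the measures is not shown. Finally, the conclusion drawn from step two does not itself promise mediated buffering, and a phase-specific indirect effect is a different estimand, not a better version of the same one. That is why both should be reported.

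**Conclusion.** The concern holds in limited form. The mediation paths as written yield an indirect effect that is the same in stricter and looser months, and so by default one on average strain during the pandemic. The phase interaction tested in step one has no matching mediation test, although the Objectives ask for mediation of associations over time. This conclusion is algebraic and rests on one inference, that strategies are measured once per person.

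Stable distress is a credible rival explanation of a level-only finding. Its size is uncertain: false mediation in about 4% of simulated studies of 75 people at a trait loading of 0.3, and 41% to 83% at 0.5 to 0.7, all on assumed values.

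**What to change.** In the mediation model, let control strategies and activation each interact with the stricter-versus-looser segments. Report two indirect effects with intervals: the phase-specific one (activation to strategies, times the strategies-by-stricter-segment coefficient) and the one on level, with the segment indicator centred so that the latter is an average over the rated months. Label the latter average strain during the pandemic, and do not read it as a mediated response to restrictions. State how often the strategy scale is administered.

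The cost is two interaction terms per neural predictor in a model already planned, with no new data. The phase-specific effect will be less precise with about 75 scanned people. By how much depends on how far people differ in phase change and how well they recall it, which the article does not say. It contrasts stricter with looser pandemic months, since no strain rating precedes March 2020, and leaves out strain common to both. It removes confounding by stable level but not confounding by whatever makes some people more reactive.

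### Objective 5 asks how networks relate to the participant's own coping, but item (5) names only tie models (ERGMs), which can show homophily and clustering and not a contribution to coping

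*Protocol article*

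**What the plan says.** Under Objectives, aim (5) is to "assess how network structure and behavioural composition relate to health-related coping and preventive behaviours during the pandemic". The network is the explanatory side and the participant's behaviour is the outcome.

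Under Data analysis, item (5) has two steps.

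- Step 1: "Social network analysis will consist of an examination of key egocentric metrics", namely "network size, density, degree centrality, and constraint", which are computed and plotted. Information on network members' vaccination, adherence and health behaviours "will be used to characterise the behavioural composition of each ego network".
- Step 2: ERGMs for small networks "will be fitted to investigate homophily in vaccination and clustering in preventive and health-related behaviour during the COVID-19 pandemic". The text adds: "Separate models will be specified for vaccination and restriction adherence as well as for health behaviours conceptualised as coping efforts".

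The item closes by assigning two conclusions to these analyses: that behavioural similarity exceeds chance, and "whether socially embedded behavioural patterns contribute to adaptive or maladaptive coping during a health crisis".

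The same section calls Objectives 4 to 6 theory-guided. Its closing paragraphs call them pre-specified and say that the analyses together will identify individual and social determinants of health behaviours and strain.

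**The concern.** The objective and the second conclusion concern the participant's behaviour. The models named in item (5) concern ties. If the plan is followed as written, Objective 5 ends with a statement about who is connected to whom, reported as a statement about what networks do for coping.

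This matters more here than it would for Objectives 1 to 3, which are labelled exploratory. A participant-level model chosen after the data are seen would not fit the pre-specified label that the article gives Objective 5. Items (2), (3) and (4) each name an outcome and its predictors; item (5) does not.

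**Working it through.** The plan states no figure on this point, so the check compares the question with the model.

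**1. What Objective 5 needs.** For participant i with own behaviour B_i, a model of the form

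g(E[B_i]) = β0 + β1 · (share of network members showing the behaviour) + β2 · (network size) + β3 · (density).

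The outcome is the participant's behaviour, and β1 to β3 answer how composition and structure relate to it.

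**2. What an ERGM gives.** P(Y = y | X) = exp{θ·s(y, X)} / κ(θ, X), where Y is the set of ties and X the members' behaviours. Ties are random and behaviour is given. With an edges term and a homophily term this is, for members j and k,

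logit P(Y_jk = 1) = θ0 + θ1 · 1{x_j = x_k}.

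θ1 > 0 says that similar members are more often tied than chance predicts. That supports the first of the two stated conclusions. It does not estimate β1 to β3, and it does not separate choosing similar contacts from being influenced by them.

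**3. Ego-alter ties.** Every network member is there because the participant named that person, so every ego-alter tie equals 1. Those dyads have no variation and hold no evidence on homophily. Only ties among the members can vary.

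**4. Adaptive versus maladaptive.** Swapping the behaviour labels replaces x with 1 − x, and 1{1 − x_j = 1 − x_k} = 1{x_j = x_k}. A uniform homophily term is therefore unchanged when the label of the behaviour is reversed.

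**5. Illustration (all settings assumed, one run each).** 150 networks, 5 members each, a binary behaviour and a generating θ1 of 0.8. There are 5 × 4 / 2 = 10 member-member dyads per network, so 1,500 in all. The model was fitted to member-member ties only.

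| Participant's behaviour generated | r with composition | Estimated θ1 | θ1, labels swapped |
|---|---|---|---|
| independently of composition | 0.04 | 0.93 | 0.93 |
| strongly dependent on composition | 0.41 | 0.87 | 0.87 |

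θ1 does not register the link between participant and network. This follows from steps 2 to 4 and not from the chosen settings.

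**6. Other models in the article.** Item (6) is the only other place where social variables enter a model: "Changes of both kinds will then be modelled as the dependent variable in several regression models including coping trajectories mentioned above", with social relations among the predictor domains. The changes meant are shifts towards the edges or centre of a distribution, used to separate accentuation from regression to the mean. That is a different outcome from the level of coping or preventive behaviour in Objective 5.

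**The case against.** The strongest reply is that this is a condensed article. Step 1 builds the metrics and composition that a participant-level model would use, so the regression may sit in a fuller plan. The sentence on separate models most naturally refers to ERGMs but does not say so. Silence alone would indeed be no finding. What remains is that the article itself names the method and assigns it a conclusion it cannot give.

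Other parts of the reply stand and limit the point:

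- The ERGMs are not misplaced. They suit the question of similarity beyond chance.
- The article does not list the ERGM terms. Pooled ERGMs could let the participant's behaviour modify density or homophily, and behaviour-specific terms would distinguish the categories, so the invariance in step 4 belongs to the uniform term only. Even then, ties remain the outcome.
- The text does not say that ego-alter ties will be modelled, so step 3 is a condition to check and not an error shown.
- The Objectives section speaks only of how networks relate to behaviour. The causal flavour comes from the closing sentence of item (5).

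A reader might infer that no model anywhere in the article links social variables to behaviour, or that Objective 5 cannot be answered with this study. Neither is supported: item (6) does use social relations as predictors, and step 1 already produces the network predictors needed.

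**Conclusion.** The concern holds in a limited form. Within item (5), the only models named are ERGMs. They can support a conclusion on homophily and clustering among network members. They do not show how network structure and composition relate to the participant's own coping and preventive behaviour, nor whether socially embedded patterns contribute to adaptive or maladaptive coping. Item (6) does not fill the gap.

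The size is qualitative. No number in the plan changes; one of three theory-guided objectives lacks a named model for its main question, and one of the two conclusions in the closing sentence of item (5) is unsupported.

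This rests on the standard definition of an ERGM and on reading the separate models as ERGMs. If they were meant to be participant-level models, saying so with outcome and predictors would largely settle the point.

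**What to change.** 1. Name, as the main Objective 5 analysis, participant-level regressions (logistic or linear by outcome type) of each own behaviour (vaccination, adherence, exercise, alcohol) on the share of network members showing that behaviour, network size and density. Interpret them as associations.
2. Limit the ERGM conclusion to homophily and clustering, and remove the claim of contribution to coping from it.
3. State whether the participant is a node in the ERGMs. If so, remove that node, because its ties are present by construction.

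The cost is a few more regressions and a more modest conclusion. The network predictors come from step 1, so no new network data are needed. This assumes that the participant's own vaccination and adherence are recorded alongside those of network members; the article leaves the full list of measures to its supplement.
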